### Sample size and statistical analysis

The sample size of 100 per cohort will have over 80% power (β of 0.80) to detect a decrease of 10% seroconversion rate in any cancer cohort (compared with assumed non-cancer population incidence of 95%) with 95% confidence (α of 0.05). T-lymphocyte correlates of vaccine response are less well-defined than the expected seroconversion rate, therefore this analysis has not been subject to formal statistical planning and comparison between groups via t-tests or analysis of variance will be for the purpose of hypothesis generation, with significant results deemed to be p < 0.05. Patient reported and medically reported toxicity will be analysed descriptively. Patient-reported quality of life will be analysed longitudinally.

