The endpoints of SerOzNET relate to these hypotheses. The core primary endpoint is seroconversion rate following COVID-19 vaccine in each cohort compared with healthy controls at 1 month post second dose. Co-primary endpoints are translational research into immune correlates of COVID-19 vaccine in each of the cancer cohorts compared with healthy controls (qualitative and quantitative measures of humoral and cellular immunity) and assessment of patient-reported and medically determined adverse effects and quality of life following vaccination. Secondary endpoints include exploratory analysis of further immunologic parameters to characterise vaccine response and investigation of durability and kinetics of response in the months post vaccination.

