### Participants

Participants are current patients of our health service (or at collaborating cancer services). The cohorts to be enrolled are:SOC or HM patients currently on cytotoxic chemotherapy.SOC or HM patients currently on immunotherapy (immune checkpoint inhibitors).(3a) SOC patients currently on systemic therapy which is not traditionally considered immunosuppressive (such as endocrine therapy, bone modifying agents or targeted therapy).(3b) Children with current or previous cancer treated only with radiotherapy, surgery, or surveillance.Patients entering survivorship after having completed a course of cytotoxic chemotherapy between 6 and 12 months ago.Patients with haematological malignancies characterised by hypogammaglobulinaemia or immunocompromise, such as multiple myeloma, CLL and low-grade lymphoma.Patients with prior allergic reactions to PEG or polysorbate-80 containing compounds (this cohort will only be analysed for safety given their heterogeneous cancer types and treatments, unless concurrently enrolled in another cohort).

Up to 100 participants will be enrolled to each arm.

Inclusion criteria are deliberately broad to allow enrolment of large representative cohorts:Age 12 years or older.Cancer diagnosis and treatment fitting one of the above study cohorts.Have not yet received a dose of COVID-19 vaccine, and eligible for vaccination as per current Australian government guidelines.

Exclusion criteria:Unfit for serial blood collection (due to frailty, concurrent illness, poor venous access or other issue as determined by investigator).Unable to consent, or parent or guardian unable to consent in the case of a patient < 18 years.Estimated survival less than 12 months.

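### The stated power of over 80% is worked out against a fixed 95% and is not established for the primary comparison with sampled healthy controls, whose number is not given

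*Protocol article*

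**What the plan says.** Under Sample size and statistical analysis, the article justifies its cohort size as follows: "The sample size of 100 per cohort will have over 80% power (β of 0.80) to detect a decrease of 10% seroconversion rate". The reference value is given as "compared with assumed non-cancer population incidence of 95"%, and the error rate is "with 95% confidence (α of 0.05"). The section names neither the test nor the sidedness for this comparison.

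Study design: the core primary endpoint is "seroconversion rate following COVID-19 vaccine in each cohort compared with healthy controls at 1 month post second dose". The same section and Setting explain that these controls are people enrolled on separate, concurrent studies, sampled at matching timepoints so that outcomes can be compared directly. The article does not state how many controls there are.

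Participants: "Up to 100 participants will be enrolled to each arm". The 100 in the power statement is therefore a maximum.

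**The concern.** A comparison of a cohort with sampled controls carries sampling error on both sides. The power statement measures the cohort against an assumed population rate, which on its face has no sampling error. Treating an estimated control rate as known makes the power look higher than it is unless the control group is large.

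The power figure is the only justification given for 100 per cohort. Readers will use it to judge what a non-significant cohort result means. If the control group were about the size of a cohort, a true 10-point deficit would be missed about one time in three (1 − 0.66 = 0.34), while the article implies less than one time in five. A cohort with a real deficit could then be taken to have a preserved response.

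**Working it through.** **Inputs.** From Sample size and statistical analysis: 100 patients per cohort, reference rate 95%, a decrease of 10% (read as 10 points, so 85%), alpha 0.05. From Participants: 100 is a maximum. Not given in the article: number of controls, test, sidedness. The number of controls is varied below as an assumption, and both one-sided and two-sided results are shown.

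**Step 1: reproduce the stated figure (one sample, fixed 95%).** Let X be the number of 100 patients who seroconvert.
- Two-sided, 0.025 in the lower tail: reject if X ≤ 89, since P(X ≤ 89 | 0.95) = 0.0115 and P(X ≤ 90 | 0.95) = 0.0282. Power = P(X ≤ 89 | 0.85) = 0.901.
- One-sided 0.05: reject if X ≤ 90. Power = P(X ≤ 90 | 0.85) = 0.945.

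Both exceed 80%, so the stated figure holds on this reading.

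**Step 2: two samples, 100 patients v 100 controls (assumed).** With p₁ = 0.85, p₂ = 0.95 and p̄ the size-weighted mean,

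power = Φ{ [ |p₂ − p₁| − z·√(p̄(1 − p̄)(1/n₁ + 1/n₂)) ] / √(p₁(1 − p₁)/n₁ + p₂(1 − p₂)/n₂) }.

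Here p̄ = 0.90. The null standard error is √(0.09 × 0.02) = 0.04243. The alternative standard error is √(0.001275 + 0.000475) = 0.04183.
- Two-sided: (0.10 − 1.960 × 0.04243)/0.04183 = 0.403, and Φ(0.403) = 0.656.
- One-sided: 0.765.

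Other standard methods at 100 v 100 (two-sided / one-sided):

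| Method | Power |
|---|---|
| Unpooled normal | 66.7% / 77.2% |
| Arcsine | 68.3% / 78.5% |
| Chi-square, exact enumeration | 68.3% / 78.6% |
| Fisher exact | 58.6% / 70.8% |

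None reaches 80%. Reading the decrease as relative (95% to 85.5%) gives 62.1% / 73.5%.

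**Step 3: equal group size needed for 80%.** n = [1.960·√(2 × 0.09) + 0.842·√(0.1275 + 0.0475)]² / 0.10² = 140.1, so 141 per group two-sided. One-sided, 111.

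**Step 4: 100 patients, varying controls (Step 2 formula).**

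| Controls | Two-sided | One-sided |
|---|---|---|
| 100 | 65.6% | 76.5% |
| 150 | 75.5% | 83.7% |
| 200 | 80.7% | 87.3% |
| 300 | 85.7% | 90.7% |
| 1000 | 92.2% | 94.9% |

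Two-sided power reaches 80% at 192 controls: p̄ = (85 + 182.4)/292 = 0.9158, null SE 0.03425, alternative SE 0.03902, so (0.10 − 1.960 × 0.03425)/0.03902 = 0.842 and Φ(0.842) = 0.800. One-sided, 120 controls suffice.

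**Step 5: fewer than 100 evaluable patients.** With 90 evaluable patients, about 222 controls are needed for two-sided 80%.

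**Step 6: detectable decrease at 100 v 100.** For 95% v 82.5% the two-sided power is 80.3%, so the detectable decrease is about 12.5 points.

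**Step 7: the label.** Power is 1 − β, so 80% power corresponds to β = 0.20. The text prints "over 80% power (β of 0.80").

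**The case against.** The strongest reply is that the power sentence names its own comparator, an assumed population rate, and that against this rate the figure is right (Step 1). That stands: on its own terms the calculation contains no arithmetic error. It does not remove the mismatch, because Study design defines the primary comparison as one with sampled controls.

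A reader might infer that the stated power is simply false and that the true power is 66%. The article does not support that. The 66% needs 100 controls, and no such number is given: 100 per cohort refers to patients, and no 1:1 ratio or cap on controls is stated. The controls come from several studies, and 192 of them (120 if the test is one-sided) would make the 80% correct.

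It can also be said that a condensed article may leave the number of controls, the test and the sidedness to the full protocol or analysis plan. Their absence alone is indeed no defect. The point here is that the article prints a power figure on one basis and an endpoint on another, so the figure cannot be taken as the power for that endpoint.

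The wrong β is a slip in a label. The words beside it make the meaning clear, so nothing numerical depends on it.

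**Conclusion.** The concern holds in this form: the stated power fits a one-sample test against a fixed 95% (exact two-sided power about 90%), and it is not established for the primary comparison with sampled healthy controls. For 95% v 85% with 100 evaluable patients and two-sided alpha 0.05, power is about 66% with 100 controls, 76% with 150, 80% with 192 and 86% with 300. At 100 v 100, no standard two-sample method tried, one-sided or two-sided, reaches 80% (range 58.6% to 78.6%).

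These figures rest on the article's own rates and alpha, on all 100 patients being evaluable, and on control numbers that are assumptions. The size of any shortfall is therefore unknown until the number of controls is stated. With about 192 or more controls (two-sided) and 100 evaluable patients there would be none.

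**What to change.** In Sample size and statistical analysis, take one of three routes:

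1. Restate the power for the two-sample comparison, giving the number of controls actually available, the test and the sidedness. If there are 100 controls, for example: with 100 evaluable patients and 100 controls, two-sided alpha 0.05, power is about 66% for 95% v 85%, and 80% for a 12.5-point decrease.
2. Commit to at least about 192 controls (about 222 if 90 patients are evaluable), provided that the parallel studies can supply them. The article does not show whether they can.
3. If a one-sample test against a fixed 95% was intended, say so, and reword the core primary endpoint in Study design to match.

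In each case, base the figure on evaluable patients, since 100 is an upper limit, and correct β to 0.20.

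The cost of routes 1 and 3 is wording. Route 1 may mean a less favourable stated power, and route 3 gives up the sampled controls as the primary comparator. Route 2 depends on control samples from the parallel studies. None of them needs extra patients.

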**Methods:**

SerOzNET is a prospective observational study of adults and children with cancer undergoing routine SARS-CoV-2 vaccination in Australia. Peripheral blood will be collected and processed at five timepoints (one pre-vaccination and four post-vaccination) for analysis of serologic responses to vaccine and exploration of T-cell immune correlates. Cohorts include: solid organ cancer (SOC) or haematological malignancy (HM) patients currently receiving (1) chemotherapy, (2) immune checkpoint inhibitors (3) hormonal or targeted therapy; (4) patients who completed chemotherapy within 6–12 months of vaccination; (5) HM patients with conditions associated with hypogammaglobulinaemia or immunocompromise; (6) SOC or HM patients with allergy to PEG or polysorbate 80. Data from healthy controls already enrolled on several parallel studies with comparable time points will be used for comparison. For children, patients with current or prior cancer who have not received recent systemic therapy will act as controls. Standardised scales for quality-of-life assessment, patient-reported toxicity and vaccine hesitancy will be obtained.

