#### Cellular immunity

The importance of T-cell-mediated immunity to optimal vaccine responses is increasingly recognised, and T-cell correlates of vaccine efficacy [including type-1 cytokine production by peripheral T cells such as interferon-gamma (IFN-γ)] have been demonstrated in early-phase trials of leading COVID-19 vaccines [28, 29]. Impaired peripheral T-cell immunological status in cancer patients is a further concern, with documented reductions in circulating T cell subsets and differences in T cell phenotypes demonstrated in this group compared with healthy controls [30]. Interestingly, in small subsets of patients Monin et al. demonstrated no clear deficiency of SARS-CoV-2-specific T-cell responses to receptor binding domain or spike antigen following prime vaccine in SOC patients compared with healthy controls although significantly worse responses were seen in a small cohort of haematological malignancy (HM) patients [24].

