Immune cell assessment of T-lymphocyte function derived from PBMC fraction will comprise phenotypic analyses of peripheral T cell subsets and functional assays to measure cytokine production (e.g., interferon γ, method previously published [47]) and cytotoxic responses (e.g., CD107a expression) after co-culture with antigen derived from SARS-CoV-2 via flow cytometry. Controls for co-culture experiments will include mitogenic stimulus and peptides derived from common viruses (such as cytomegalovirus, Epstein–Barr virus, or influenza antigen in patients who have received influenza vaccine). Correlation of magnitude of serological response and T-cell assays will be described within study cohorts and between cohorts with healthy controls, to estimate impact of immunological aspects of disease and treatment on vaccine response. Recent data in immunocompromised patients on rheumatological disease modifying agents showed comparable immune cellular response to COVID-19 vaccine to controls, despite reduced rate of neutralising antibodies, suggesting potential heterogenous cellular and humoral immune response to vaccine in immunocompromised patients [48]. PBMCs will also be analysed for epigenetic markers of T cell dysfunction, effector status, and exhaustion.

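### T-cell correlates are ranked co-primary but planned as unplanned, hypothesis-generating tests with a significance threshold, and the named tests give the collected baseline sample no role

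*Protocol article*

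**What the plan says.** **Rank of the endpoint.** In the Protocol article, Study design, seroconversion at 1 month after the second dose is the core primary endpoint. The next sentence adds: "Co-primary endpoints are translational research into immune correlates of COVID-19 vaccine in each of the cancer cohorts compared with healthy controls". Its bracket spells out what is covered: "qualitative and quantitative measures of humoral and cellular immunity". Adverse effects and quality of life are also co-primary. Exploratory analysis of further immunologic parameters is listed separately, under secondary endpoints.

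**Status and method of the analysis.** The section Sample size and statistical analysis describes the T-lymphocyte part differently. On its planning, the section states that "this analysis has not been subject to formal statistical planning". On the tests to be used and their purpose, it goes on: "comparison between groups via t-tests or analysis of variance will be for the purpose of hypothesis generation". It nevertheless attaches a threshold to those tests, in these words: "with significant results deemed to be p < 0.05". Power is calculated for seroconversion only.

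**Baseline.** The abstract says blood is "processed at five timepoints (one pre-vaccination and four post-vaccination"; the Blood collection section and its sampling table confirm the baseline draw. The Cellular immunity section reports, for cancer patients, "documented reductions in circulating T cell subsets and differences in T cell phenotypes demonstrated in this group compared with healthy controls". No section says how the baseline sample enters the T-cell comparison.

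**The concern.** Two things are at stake.

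The first is what the trial may claim. A co-primary endpoint is normally one on which a study draws a confirmatory conclusion. An analysis without formal planning, run to generate hypotheses, cannot support one. Because the article keeps a separate place for exploratory immunology among the secondary endpoints, the co-primary rank reads as deliberate. Adding a significance threshold to the same analysis invites readers to treat any p < 0.05 among several cohorts and many T-cell readouts as a primary result. The Discussion expects all of the findings to be likely to influence practice on vaccine timing, type and boosters, so the label matters.

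The second is interpretation. The groups are not randomised and the healthy controls come from parallel studies, so baseline differences between groups are to be expected. A t-test or ANOVA of post-vaccine values alone could not separate a deficit that existed before vaccination from a weaker response to the vaccine. The baseline sample needed to separate them is already being collected.

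**Working it through.** **1. The plan's own figure.** The article gives no sample size, standard deviation or power for any T-cell endpoint, so there is nothing to reproduce there. Its one calculated figure, over 80% power with 100 per cohort, concerns seroconversion and does not bear on this point.

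**2. The statements side by side.**

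| Item | Study design | Sample size and statistical analysis |
|---|---|---|
| Cellular immunity v healthy controls | Co-primary | No formal statistical planning |
| Purpose | Ranked above the exploratory work listed as secondary | Hypothesis generation |
| Decision rule | None given | p < 0.05 called significant |

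A fuller analysis plan could add detail, but both statements are made in this article and one of them has to be reworded.

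**3. Multiplicity, if separate t-tests are used.** The sixth cohort (allergy to PEG or polysorbate 80) is analysed for safety only unless its members also belong to another cohort. That leaves five cohorts for immune comparisons.
- Independent tests at 0.05: 1 − 0.95^5 = 0.226.
- Five cohorts against one shared control group of equal size, where the test statistics correlate at 0.5: about 0.18.

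This is per assay and per timepoint. The equal control size is an assumption, because the article does not give the number of controls.

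**4. Baseline carry-over, if only post-vaccine values are compared.** The article gives no baseline gap, no baseline-to-post correlation and no control numbers. The following are assumptions: 100 v 100, two-sided 0.05, baseline gap d of 0.2 to 0.5 SD, correlation r of 0 to 0.7, and no group difference in the post-vaccine mean once baseline is given.
- Bias of the post-only contrast, in SD units: r × d.
- Expected z: r × d × √(100/2) = r × d × 7.071.
- Rejection probability: Φ(z − 1.96) + Φ(−z − 1.96).

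Example: d = 0.5 and r = 0.7 give a bias of 0.35 SD, z = 0.35 × 7.071 = 2.475, and rejection of 0.697.

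| | r = 0 | r = 0.3 | r = 0.5 | r = 0.7 |
|---|---|---|---|---|
| d = 0.2 SD | 5% | 7.1% | 10.9% | 16.8% |
| d = 0.5 SD | 5% | 18.5% | 42.4% | 69.7% |

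Under the same null, a baseline-adjusted comparison stays at about 5%. It multiplies residual variance by 1 − r²: 0.91, 0.75 and 0.51 for r = 0.3, 0.5 and 0.7.

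**5. Where carry-over is plausible.** The Analyses section plans T-cell subset phenotyping, cytokine and CD107a responses, and epigenetic markers of dysfunction, effector status and exhaustion. Subset, phenotype and exhaustion measures exist before vaccination whatever the exposure, so a non-zero r is most plausible for them. For responses specific to SARS-CoV-2 it is less so: participants are unvaccinated at entry, and confirmed infections were below 0.2% of the population when enrolment began. Baseline signal may then be low, and the left of the table is nearer the mark. That last step is inference, not something the article states.

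**The case against.** The strongest reply is that the article is open about the T-cell work. Seroconversion is called the core primary endpoint, it alone is powered, and the T-cell comparisons are declared hypothesis-generating. That limits the harm but does not remove the conflict, because the same comparisons are still called co-primary and still given a significance threshold.

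A reader might infer that the plan ignores the baseline sample, or tests raw post-vaccine values. The text does not support this. It names a family of tests, not the variable tested; a t-test or ANOVA can be run on change or on log values, and a condensed article may leave that to the full protocol or analysis plan. Nor does the clause reach antibody titres: it concerns T-lymphocyte correlates only. What stands is narrower. No baseline term is named where the article itself gives reason for one.

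The multiplicity figure also has limits. ANOVA gives one global test per assay, so the 18% applies only to separate t-tests. Toxicity is analysed descriptively and quality of life longitudinally, neither with a threshold, so the multiplicity argument does not touch them.

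It is also fair to say that pre-existing impairment is part of the question. The Analyses section wants to estimate the impact of disease and treatment on vaccine response, and conditioning on baseline could remove some of that effect. This stands, and it is why the unadjusted contrast should be kept beside the adjusted one.

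Finally, "Controls for co-culture experiments will include mitogenic stimulus and peptides derived from common viruses" may help separate general T-cell weakness from a vaccine-specific deficit. The article does not say that these controls enter the group comparison.

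**Conclusion.** The conflict between the co-primary rank and the unplanned, hypothesis-generating analysis with a significance threshold is on the page and rests on no assumption. It should be resolved. As a measure of what the threshold would carry, five separate t-tests against a shared control group of equal size have a family-wise error of about 18% per assay (23% if independent).

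The baseline point is a risk to close, not a demonstrated error. It applies if post-vaccine values are compared alone, and most plausibly to subset, phenotype and exhaustion measures. Its size cannot be computed from the article. Under the assumptions shown, false rejection lies anywhere from 5% to about 70%. A reader might take the upper end as the expected error, or conclude that prior T-cell differences would be reported as poor vaccine response. The article supports neither: both need a baseline gap and a correlation that it does not give.

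**What to change.** - Reconcile the Study design and statistical sections. Keep seroconversion at 1 month after the second dose as the single confirmatory primary endpoint and label the T-cell correlates secondary or exploratory.
- Report T-cell comparisons as estimates with confidence intervals, and drop the significance label for them.
- State that T-cell comparisons use the participant's own baseline value, by ANCOVA or a mixed model, on the log scale where the measure is skewed. Report the unadjusted post-vaccine contrast alongside, and say which question each answers.

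The cost is wording and modest extra analysis, since the baseline blood is already drawn. A rule is needed for participants or controls without a usable baseline sample.

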### Ethics approval, trial registration and current status

This protocol was submitted to the Monash Health Human Research Ethics Committee (HREC) on 26 May 2021, and the amended final version (2.0) was approved on 22 June 2021. The trial was submitted for registration with the Australian New Zealand Clinical Trials Registry (registration number ACTRN12621001004853) in June 2021 prior to enrolment of first participant, with registration number granted on 30 July 2021. The first patient was enrolled on 25 June 2021. Recruitment is ongoing.

